#### Accuracy of Ocular Pulse

In the first stage of this analysis each instance of parallel HR and TF recording will be coded as 1 (“success;” Ocular Pulse as measured by TF is within ± 15% of HR measured directly) or 0 (“failure;” otherwise). Assessment of success or failure will be done by comparing HR measured directly to the thirty-second TF recording in the interval HR was measured. If two TF recordings are obtained during the six (6) minutes of direct HR recording, that most overlapping with the HR recording will be chosen. If both TF measurements show the same overlap with HR, both will be used.

The second co-primary endpoint will then be tested via the following hypotheses:

H_0_: π_accuary_ < 0.70

H_1_: π_accuary_ ≥ 0.70

Where,

π_accuary_ – is the proportion of Ocular Pulse values for one minute intervals that are within ± 15% of HR measured directly

Hypotheses will be tested by constructing a 95% two-sided confidence interval using SAS^®^ PROC GLIMMIX (logistic link function) to account for possible dependency between measurements taken from the same individual.

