## Sample Size Considerations

This study has two co-primary endpoints so that presentation of sample size is based on demonstrating:

- A significant, positive and linear correlation between TF recordings and time during the wake/sleep period.
- Proportion of accurate TF Ocular Pulsation recording relative to HR (TF within ± 15% of HR) is at least 70%; i.e. 70% is an objective performance criterion (OPC) for demonstrating accuracy of Ocular Pulsation

We wish to have at least 90% power to show both of the above, implying 95% power for rejecting each null hypothesis (0.95 * 0.95 = 0.90, conservatively assuming independence of measurements done for testing the two hypotheses).

Previously collected data provide our best estimate for true linear relationship between TF and Time at 0.708 with a standard deviation of 0.285. After Fisher-z transformations of individual correlations we obtain a mean of 1.073 with standard deviation of 0.544. Given these estimates and using a one-sample t-test versus a null of no correlation, a sample size of 10 provides over 95% power to reject the null for this hypothesis.

At this stage we estimate that on 90% of one-minute thirty-second recordings Ocular Pulse as detected by TF will be within ± 15% of HR measured directly. To demonstrate 0.90 ≥ 0.70 with 95% power requires 53 independent observations using two-sided Exact Binomial confidence interval. In this study, each subject will contribute three (3), one-minute TF_Ocular Pulse_/HR relationships. While within-subject TF-HR agreement is not likely to be independent, we assume at this stage that 90 such observations, obtained from 30 subjects, will provide requisite power; i.e. will provide the equivalent of at least 53 independent observations. As described below, confidence interval will be computed using a mixed logistic model (SAS^®^ PROC GLIMMIX) to account for dependencies in the data. Simulations will be used to assess the assumption that 90 observations from 30 subjects provide at least 95% power. If simulations will indicate that more than 30 subjects are needed, this protocol will be amended accordingly before initiation of trial.

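### The ocular-pulse test concerns a population proportion, but the named mixed logistic model, taken in its ordinary sense, gives an interval for a median subject

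*Protocol*

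**What the plan says.** Protocol section 9.8.4 (Accuracy of Ocular Pulse) codes each parallel TF and heart-rate recording as success or failure. It sets the null hypothesis at an accuracy below 0.70 and defines the parameter thus: it "is the proportion of Ocular Pulse values for one minute intervals that are within ± 15% of HR measured directly". The method follows: "Hypotheses will be tested by constructing a 95% two-sided confidence interval using SAS" PROC GLIMMIX with a logistic link, to allow for dependence within a subject.

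Section 9.7 (Sample Size Considerations) fixes the threshold: "70% is an objective performance criterion (OPC) for demonstrating accuracy of Ocular Pulsation". It assumes a true accuracy of 90% and says that showing this "with 95% power requires 53 independent observations using two-sided Exact Binomial confidence interval". The trial plans 90 observations, three from each of 30 subjects, assumed to be worth at least 53 independent ones. On the analysis it says that the "confidence interval will be computed using a mixed logistic model". It also promises simulations of the 95% power assumption, with an amendment before the trial starts if more subjects are needed.

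Neither section gives the random-effects structure, the estimation method or the back-transformation. No between-subject variance is stated.

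**The concern.** The parameter and its sample size are marginal: the share of all readings, over all subjects, that are accurate. A logistic model with a subject random effect has a different natural target. Its back-transformed intercept is the success probability of a subject whose random effect is zero, that is, a median subject. Because the logit link is non-linear, the two agree only when subjects do not differ. Above 0.5 the median-subject value is the larger.

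The protocol chose the model because it expects dependence within subjects, and that is the condition under which the two quantities separate. A co-primary claim against a fixed 70% criterion would then rest on an interval for something other than the parameter in the hypothesis, with an optimistic reported accuracy. The error rate and power would depend on a fitting method that is not stated.

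**Working it through.** **1. The plan's own figure.** Inputs from section 9.7: null 0.70, truth 0.90, 95% power, two-sided 95% exact interval. With n = 53, the Clopper-Pearson lower limit first exceeds 0.70 at 44 successes. P(X ≥ 44) is 0.0233 under 0.70 and 0.9645 under 0.90. With n = 52 the power is 0.929. The 53 is reproduced, and it refers to a marginal proportion.

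**2. How much dependence the plan tolerates.** 90 / 53 = 1.70 is the largest design effect allowed. With three readings per subject, 1 + (3 − 1) × ICC = 1.70 gives an ICC of about 0.35.

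**3. Median-subject value against population value.** Assume logit(p) = b + u, with u normal, mean 0 and SD s. The population proportion is E[expit(b + u)], the median-subject value is expit(b), and ICC = Var(p) / [π(1 − π)]. Solve for b so that the population proportion is fixed, by Gauss-Hermite integration. The SD is an assumption, shown as a range.

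| SD (logit) | ICC at π = 0.70 | Median subject, π = 0.70 | Median subject, π = 0.90 |
|---|---|---|---|
| 0 | 0 | 0.700 | 0.900 |
| 1 | 0.16 | 0.735 | 0.929 |
| 1.5 | 0.27 | 0.766 | 0.950 |
| 2 | 0.38 | 0.800 | 0.968 |

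Example: at SD 1 and π = 0.70, b = 1.018 and expit(1.018) = 0.735. Conversely, a median-subject value of 0.70 corresponds to a population proportion of 0.669, 0.646 and 0.626 at SD 1, 1.5 and 2. The tolerated ICC of 0.35 is reached at an SD of about 1.9 when π = 0.70 (median subject about 0.79) and about 2.4 when π = 0.90 (about 0.98).

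**4. Effect on the test.** 5,000 simulated trials per setting, 30 subjects with 3 readings each. Success is a lower 95% limit (t, 29 df) above 0.70. Three analyses: random intercept by maximum likelihood (ML) with the intercept back-transformed; the same by pseudo-likelihood (PL); and the marginal proportion with a cluster-robust standard error on the logit scale.

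| SD | Type I error at 0.70: ML / PL / marginal | Power at 0.90: ML / PL / marginal |
|---|---|---|
| 0 | 0.013 / 0.016 / 0.020 | 0.985 / 0.995 / 0.997 |
| 1 | 0.017 / 0.026 / 0.020 | 0.962 / 0.981 / 0.984 |
| 1.5 | 0.026 / 0.038 / 0.019 | 0.913 / 0.956 / 0.963 |
| 2 | 0.031 / 0.045 / 0.020 | 0.823 / 0.897 / 0.931 |

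Nominal one-sided error is 0.025. Median estimates at a true 0.70 and SD 0, 1, 1.5 and 2 are 0.711, 0.734, 0.762 and 0.799 with ML, and 0.701, 0.710, 0.717 and 0.725 with PL. The sample proportion averages 0.70 throughout. PL fits that did not converge (8.8% at SD 2 and true 0.90) count as failures. A further simulation put ML power at SD 2 at 0.81.

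**The case against.** The strongest reply is that the protocol does not fix the faulty step. It never mentions a random intercept or says how the interval is brought back to the probability scale. PROC GLIMMIX can fit a marginal model through an R-side covariance, which would match the wording of section 9.8.4, and model syntax is often left to an analysis plan. This stands in part: the fault is conditional. But section 9.7 names a mixed model, which ordinarily means subject random effects, and nothing in the protocol asks for a population-averaged interval.

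A reader might infer that a device with 70% accuracy would readily be declared a success. The figures do not support that. Success depends on the lower limit, and the random-effects interval is also wider. Type I error stays near nominal with ML and reaches about 4.5% with PL at SD 2. Nor do the largest effects come from one method: the larger overstatement and power loss belong to ML, the larger error rate to PL.

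A reader might also infer that the 53 is wrong or that this choice alone costs the planned power. The 53 is correct for its inputs, the marginal analysis also falls to 0.93 at SD 2 because of clustering, and section 9.7 leaves power under the model to pre-trial simulation. However, a simulation of power alone would not show that the interval is for a different quantity.

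**Conclusion.** The point holds conditionally. The hypothesis, the criterion and the sample size concern a population proportion. The named model, fitted with subject random effects and back-transformed at the intercept, estimates a median subject's accuracy.

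The overstatement of the model's target at a true 0.70 runs from nothing at SD 0 to about 10 percentage points at SD 2, roughly the limit of the dependence that the sample size tolerates. With pseudo-likelihood the typical estimate is only about 2.5 points too high at SD 2 (0.725). The effect on the type I error is modest, and at SD 2 the power lost relative to a marginal analysis is about 11 points with ML (0.823 against 0.931) and 3 with PL (0.897 against 0.931).

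All of this rests on an assumed between-subject SD and a normal random effect. If subjects do not differ, the two targets coincide. It merits correction because it bears on a co-primary decision and a better-matched analysis is available at little cost.

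**What to change.** In sections 9.7 and 9.8.4, state that the 95% interval is for the population-averaged proportion. Obtain it by logistic GEE, or by GLIMMIX with an R-side covariance and no random intercept. In either case use subject as the cluster and small-sample-corrected empirical standard errors. Integrating the mixed-model estimate over the random effect is an acceptable alternative. Define success as a lower limit above 0.70.

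State a fallback for data without any failures, where the logit-scale interval breaks down. One choice is the exact interval with subjects as units: for 30 of 30 subjects its lower limit is 0.025^(1/30) = 0.884.

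Run the promised pre-trial simulations with this estimator over a stated range of between-subject variance, reporting type I error at 0.70 as well as power at 0.90. The cost is protocol wording and a different SAS call; no new data are needed. If the simulations show that 30 subjects are too few, section 9.7 already provides for an amendment.

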### Secondary Efficacy

Diurnal Rhythm: Prior to the trial, 24-hour diurnal IOP rhythm types will be identified in the literature. Evaluators will then be trained to categorize subjects’ 24-hour TF recording into these rhythms types. A protocol for this training, and statistics used for its evaluation (e.g. Kappa for agreement between raters), will be presented separately.

Each subject in the trial with at least 80% valid TF data will be categorized as having one of the diurnal IOP rhythms by two independent raters. Rater agreement will be described using a K x K confusion matrix, K being the number of rhythm types identified. Cohen’s Kappa will be computed for this table and presented along with two-sided 95% confidence intervals.

Subject Acceptance: Subject Acceptance of TF will be measured by questionnaire and presented descriptively, including mean along with associated two-sided 95% confidence interval.

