### Secondary Efficacy

Secondary efficacy endpoints include, for each subject:

- Subject Acceptance of TF, which will be measured on a 5 point analog scale where 5, indicates high acceptance of TF and 1 indicates low acceptance.
- Categorization of subject diurnal rhythm of IOP as measured by TF and assignment to pre-specified diurnal rhythms identified from the literature.

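### The diurnal-rhythm efficacy endpoint is summarised only by agreement between two raters on the same TF trace, so it describes reader reliability and gives no evidence that the 24-hour trace follows IOP

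*Protocol*

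**What the plan says.** Protocol Sections 5.2.3 and 9.5.3 list as a secondary efficacy endpoint: "Categorization of subject diurnal rhythm of IOP as measured by TF and assignment to pre-specified diurnal rhythms identified from the literature".

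Section 9.8.5 fixes the analysis:

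- **Who is classified:** "Each subject in the trial with at least 80% valid TF data".
- **What is read:** "Evaluators will then be trained to categorize subjects’ 24-hour TF recording into these rhythms types".
- **How subjects are assigned:** each such subject "will be categorized as having one of the diurnal IOP rhythms by two independent raters".
- **Table:** "Rater agreement will be described using a K x K confusion matrix, K being the number of rhythm types identified".
- **Statistic:** "Cohen’s Kappa will be computed for this table and presented along with two-sided 95% confidence intervals".

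Only the rater training is deferred: "A protocol for this training, and statistics used for its evaluation (e.g. Kappa for agreement between raters), will be presented separately". The rhythm types and the value of K are not listed. No hypothesis, kappa threshold or success rule is given.

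Elsewhere, Section 7.6 says that TF measures will be compared with parallel IOP in the fellow eye. Section 10 gives the purpose of the investigation as correlating conventional tonometer values with TF output. Sections 7.3 and 7.4 schedule fellow-eye pneumatonometry about every two hours through the recording, sitting when awake and supine in bed.

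**The concern.** The endpoint is called efficacy and is worded as a rhythm of IOP, but the analysis never brings in IOP. It asks whether two trained people put the same label on the same trace. Because the table has exactly as many rows and columns as there are literature rhythms, it has no place for a trace that resembles none of them, and such a trace would be reported under the name of an IOP rhythm.

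What is at stake is interpretation. The intended use in Section 1.2 is recording the timing of relative IOP changes for up to 24 hours. The wake/sleep co-primary covers 8 hours and the ocular-pulse co-primary uses short recordings. This is therefore the only efficacy endpoint built on the full 24-hour trace. A reader of the final report could take a filled table and a good kappa as support for 24-hour IOP tracking, which the analysis does not supply.

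**Working it through.** **No stated figure to reproduce.** The protocol gives no K, kappa target or power for this endpoint.

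**Structural argument, free of assumptions about the traces.** Let X be a subject's TF trace, and R1(X) and R2(X) the two raters' categories. The table counts pairs (R1(X), R2(X)), and

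κ = (p_o − p_e) / (1 − p_e),

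where p_o is the observed proportion on the diagonal and p_e the proportion expected from the margins. Now reassign the TF traces at random among the classified subjects, so that no trace belongs to the eye it is attributed to. The same pairs are counted, so the table, p_o, p_e and κ are all exactly unchanged. A statistic that does not change when the traces are detached from the subjects' own IOP cannot be evidence that a trace follows that IOP.

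**Reference data at hand.** Two-hourly readings over 24 hours give about 24 / 2 = 12 fellow-eye values per subject. Section 9.4.1 uses four of them (two before and two after going to bed), to select subjects for the wake/sleep analysis. No stated analysis uses the 24-hour profile to classify rhythm.

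**How large can kappa be without IOP content?** This is an illustration only. The 30 subjects come from Section 9.7; everything else is assumed:

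- 288 points per trace, that is 24 × 60 / 5, from the five-minute activation cycle in Section 9.2.
- K cosine templates differing in phase.
- Each rater scores the correlation of the trace with each template, adds independent normal error (SD 0.1, 0.2 or 0.4 on the correlation scale), and picks the highest.

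With TF generated as a random walk independent of IOP (300 runs), mean inter-rater kappa was:

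| K | error 0.1 | error 0.2 | error 0.4 |
|---|---|---|---|
| 3 | 0.89 | 0.77 | 0.54 |
| 4 | 0.85 | 0.68 | 0.43 |
| 5 | 0.77 | 0.57 | 0.34 |

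In the same runs, mean kappa between the TF category and the IOP category lay between −0.01 and 0.02 (SD across runs 0.08 to 0.14).

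**Where high kappa fails to appear.** With white noise in place of drift (400 runs, same error model), mean inter-rater kappa at K = 4 was 0.15, 0.05 and 0.01, and it was no more than about 0.2 for any K from 3 to 6. Even with drift, at the largest rater error kappa exceeded 0.4 in only about six runs in ten at K = 4, and in fewer than one in three at K = 5.

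**The case against.** The strongest reply is that this endpoint was never meant to validate the device. Section 7.6 first describes the fellow-eye comparison under the primary objective, and then adds subject acceptance and rhythm categorisation. Acceptance sits under the same secondary efficacy heading and is not a measure of IOP validity either. Whether readers classify a 24-hour profile consistently is a fair question for such a device. Much of this stands: inter-rater kappa is worth reporting and should be kept. It does not remove the mismatch between an endpoint worded as a rhythm of IOP and an analysis into which IOP does not enter.

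Three stronger readings are tempting, and the protocol does not support them:

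- **That the endpoint would succeed for a device that does not work.** Section 9.8.5 only describes agreement. Where the protocol intends a success rule, as in Section 9.8.4, it states one.
- **That every subject is forced into a rhythm.** Only subjects with at least 80% valid TF data are classified. The unlisted types might also include a flat or irregular one, which would partly serve as a residual class.
- **That a meaningless signal must give high kappa.** Smooth drift with a readable shape can, but noise could well give a low one and so be exposed.

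It is also fair to object that the tonometer profile is a weak reference. It has about 12 points, posture changes from sitting to supine, and the fellow-eye correlations cited in Section 10 run from 0.65 to 0.73 (mean 0.70). This limits what an added comparison can show. It is a reason to keep that comparison descriptive, not a reason to omit it.

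**Conclusion.** The point holds in a limited form. As fixed in Section 9.8.5, the endpoint describes reader reliability and gives no evidence that the 24-hour TF trace follows IOP. The protocol states that comparison as its aim and collects data that could address it. The lack of a stated not-classifiable option adds to the problem, subject to what the unlisted rhythm types turn out to be.

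The structural conclusion rests only on the raters reading the TF trace and nothing else, which is what the protocol describes. The kappa range of 0.34 to 0.89 for drift unrelated to IOP rests on assumed templates, drift and rater error. It shows that moderate to high kappa is possible, not that it is expected. The endpoint is descriptive and secondary, and neither the co-primary conclusions nor the sample size is affected. It should be corrected, but it does not threaten the trial.

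**What to change.** In Section 9.8.5:

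1. Add a none / not-classifiable category, use a (K+1) × (K+1) table, and report the proportion of classified subjects assigned to a recognised rhythm.
2. Label inter-rater kappa as reader reliability.
3. Add a descriptive analysis in which the same raters, masked to subject identity and to the TF trace, classify each subject's fellow-eye 24-hour pneumatonometer profile. Report agreement between TF and tonometer categories as kappa with a 95% confidence interval, beside the inter-rater kappa.
4. State with the result that two-hourly sampling, the sitting-to-supine change and a fellow-eye correlation of about 0.70 limit attainable agreement, so that low agreement cannot be attributed to the device alone.

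The cost is a wording change, a second rating session and brief rater training on tonometer curves. No new measurements on subjects are needed. The TF-versus-tonometer figure is likely to look less favourable than inter-rater kappa.

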### Performance

Validity rate of TF measurements will be computed per subject. Descriptive statistics will then be provided over all subjects, including two-sided 95% confidence intervals for the mean.

## Interim Analysis

No interim analysis is planned in this trial.

# scientific analysis of the protocol

SENSIMED Triggerfish^®^ is a device intended for continuous IOP fluctuation monitoring. The system consists of several parts, of which the Sensor is based on a soft silicone contact lens integrating microelectronic components. A circular strain gage senses variations in central corneal curvature that have been shown to be related to changes in IOP. Like with tonometers that detect IOP through surrogate variables, there is a need to determine how the surrogate variable relates to the monitored property.

Leonardi et al have shown excellent linearity and repeatability during monitoring of fluctuating IOP in pressure-controlled, enucleated porcine eyes. In enucleated eye, however, whether animal or human, corneal properties such as elasticity and hydration status are significantly altered compared to in vivo eyes. Phenomena such as eye blinks and circadian CCT variation are absent. Further, appropriate corneal hydration and post-lens liquid film cannot be maintained artificially for periods extending beyond a few minutes. Specific investigation of the relationship between IOP and SENSIMED Triggerfish^®^ output signal is therefore of interest in vivo.

It is the purpose of this investigation to correlate IOP values obtained with a conventional tonometer to the output provided by SENSIMED Triggerfish^®^.

While IOP cannot be measured on an eye with the SENSIMED Triggerfish^®^, it *can* be measured on the fellow eye. For this to be meaningful there needs to be a relationship between the two eyes in glaucoma patients. Studies show that while the correlation in IOP between fellow eyes is far from perfect, it is clinically meaningful. Specifically, Dinn et al report that about 76% of fellow eyes were, on average in a given 3-hour interval, within 2mmHg of each other; 87% were within 3mmHg of each other. Dinn et al conclude that "diurinal IOP profiles between fellow eyes are parallel in POAG patients." Moreover, the similarity is greater in treated relative to untreated patients. They do however concede that this relationship has its limitations and that in up to 20% of treated patients there will be an asymmetric relationship between fellow eyes of 3mmHg or more. It is however important to note that 3mmHg is within the error or measurement of GAT.

Sit et al report a weaker relationship to that described in the preceding paragraph. At the same time, they found that correlation between fellow eyes under different conditions (e.g. office-hour sitting, diurnal supine) ranged between 0.65 and 0.73 (mean r = 0.70) and was significant. Additionally, about 85% of fellow eyes were within 3mmHg on a given measurement time point. Sit et al divided the day into 4 periods and computed mean, peak and trough IOP values for each. When averaged over all subjects, fellow eyes never differed by more than 1mmHg for any of these parameters.

In conclusion, it appears that fellow eyes can provide reasonable surrogate IOP measurements for one another.

Based on the above considerations, we consider this investigation as scientifically sound.

